### Breaking the cluster intervention code

Breaking the cluster intervention code necessarily occurred after randomization (see above) so that training could be organized at the clusters. However, only key people involved with the organization and delivery of the training were informed of the intervention/training schedule.

### Quantitative methods

#### Design

The original study protocol (as documented in the Australian New Zealand Clinical Trials Registry, or ANZCTR) was developed over a period of 18 months and involved consultation with the Chief Investigators (CIs) and local stakeholders, and included representation from primary care, community care, and patients. The planning team included primary care academics familiar with the known barriers associated with recruitment of GPs into research projects [40–42].

The research team originally planned to deliver the recovery-oriented practice training intervention to one participating GP per cluster site, and to evaluate the process using a study design of a cRCT conducted over four years, utilizing a two-step stepped-wedge design. This design was developed to combine the rigor of a cluster randomized trial with the pragmatic approach of the stepped-wedge design to implement the intervention at all sites. However, initial challenges with GP engagement and patient recruitment resulted in necessary modifications to the original project protocol. These are outlined below. All adaptations to the study protocol were considered by, and required the approval of, the appropriate Module Committee governing the relevant aspect of the project (see *Study leadership* section). Half-yearly project reports to the funding body also advised of changes made or intended. In each case these were then considered by the agent of the funding body. Queries as raised in some cases were responded to by the investigators prior to acceptance of the report by the funding body agents. Adaptations to the original protocol as reported here were thereby given endorsement from the funding body. Despite the adaptations described below, the basic two-step stepped-wedge cRCT design remains unchanged (see Fig. 1) and the trial will conclude within the planned four-year timeframe.

#### Adaptations to design

Delays in recruitment of GPs and patients and in delivery of the intervention required some modification to the design in order to be able to deliver the project outcomes within the allowed project duration. Cluster definition was broadened to include one or more GPs from each site in an effort to boost recruitment. As well, study steps were reduced from 12 months to 9 months. Based on the Kirkpatrick training evaluation model [43], the 9-month step period is an acceptable time point for the measurement of change. It allows 3 months for consolidation and a 6-month period for patients to be exposed to GPs implementing recovery-oriented practice.

#### Measures

All outcome measures are listed in Table 1, and the study survey is available upon request to the contact author. The primary outcome measure, the 22-item Questionnaire about the Process of Recovery (QPR) [44], enables an examination of the primary research question by collecting information from patients of participating GPs about personal recovery. This patient-rated outcome measure was chosen for the study end-point as personal recovery is experienced by an individual rather than assessed by an expert.

**Table 1 Tab1:** Primary, secondary and other outcome measures in PULSAR Primary Care

Patient survey (quantitative) measures	
Primary outcome	1. Questionnaire about the Process of Recovery (QPR) [44]
Secondary outcomes	2. INSPIRE questionnaire [45] 3. Warwick-Edinburgh Mental Well-being Scale (WEMWBS) [46] 4. Kessler Psychological Distress Scale (K10) [47]
Other measures	5. Participant Demographic Record 6. General-practice-Users Perceived-need Inventory (GUPI) [48] 7. Health economic and service utilization questionnaire
Patient qualitative data	
Interviews	Individual interviews
Focus groups	Focus groups
GP qualitative data	
Interviews	Individual interviews
Focus groups	Focus groups

The secondary outcome measures include the importance of services in recovery questionnaire (INSPIRE) [45], which assesses the recovery orientation of the GP service from the perspective of the patient, and two measures of mental health and wellbeing, the Warwick-Edinburgh Mental Well-being Scale (WEMWBS) [46], and the Kessler Psychological Distress Scale (K10) [47].

Additional measures are: Participant Demographic Record and the General-practice-Users Perceived-need Inventory (GUPI) [48]. As well, a section in the survey is designed to gain an understanding of any financial burden of illness as well as the participants’ use of health services. These health economic and service utilization questions, which contain both study-specific items and questions adapted from the 2007 Australian National Survey of Mental Health and Wellbeing [49], include information on the participants’ job status, income, consultations with health professionals, medications being taken, admissions to hospital, and any time away from usual roles because of illness. Participants are advised that if they cannot answer a question precisely, then to provide a best estimate and that there are no ‘right’ or ‘wrong’ answers. Finally, where specific consent is provided, information related to diagnosis, mental health status and current medication is also collected from GP medical records.

#### Sample size targets

The study has two sample groups: GPs and patients of these GPs. Sample size calculations were done using Stata statistical software *stepped-wedge*: for clusters defined at the level of the general practice site, the primary outcome measure is the QPR, with a published mean of 46 and standard deviation of 16, power of 0.80, significance level set at 0.05, intraclass correlation coefficient (ICC) within practice sites of 0.05, the number of steps (2), and patient data collected cross-sectionally at three time points (baseline, Step 1, and Step 2).

The original sample target was a minimum of 20 different sites (clusters) with one GP per site; each GP was required to recruit a minimum of 30 patients during the four-year project (10 patients at baseline, 10 at Step 1, and 10 at Step 2), resulting in a minimum of 600 patient participants overall.

#### Adaptations to sample size targets

Challenges in engaging GPs and recruiting patients were encountered at the beginning of the project (see earlier and also below). As a result, the protocol was adapted so that more than one GP from each cluster can participate. Each participating GP is still expected to recruit a minimum of 30 patients over the duration of the trial; therefore, if there are two participating GPs at a cluster, each will recruit 30 patients, resulting in 60 patients for that cluster. This efficiency of scale appears to be working well in some clusters. The required cluster number was also reduced from 20 to 10 plus. These sample numbers will be sufficient to detect a medium to medium-large effect in the primary outcome.

#### GP recruitment

Over 325 general practice and community health centers in the Monash Health catchment area were identified by the research team, using the National Health Services Directory and the telephone directory. The team also accessed a comprehensive database of GPs who have been involved in GP research in the south-east region of Melbourne held by the Department of General Practice at Monash University. Existing contacts within relevant health care organizations that coordinate service delivery related to primary care, such as the Medicare Locals were utilized. As noted earlier, since this phase of the study, these organizations have been replaced by Primary Health Networks.

An *Invitation to Participate Letter* was sent to each potentially eligible GP site, which outlined the study and requested participation. The letter was addressed to the lead physician(s), owner(s), or manager at each address and was signed by the project Principal Investigator (PI) and two CIs (both general practitioners). Letters of invitation to the community health centers also included a letter of support from Monash Health, who governs the centers. A PULSAR team member made follow-up telephone calls four-to-seven days after letters were posted to explore interest and, if appropriate, request a meeting with senior site staff to explain the study further. If a GP decided to participate, she or he was required to sign the GP Participant Information and Consent Form.

Simultaneously, the study was advertised and GP participation sought using various newsletters and websites.

#### Adaptations to GP recruitment and retention

In addition to allowing more than one GP per cluster site to be recruited and expanding the geographical area of participating practices, as mentioned above, increased efforts were made to engage the Medicare Locals in promoting the study. This led to a sufficient number of GPs (*n =* 30) being recruited.

#### Patient recruitment

Participating GPs are responsible for organizing patient recruitment at their site. Recruitment is coordinated by the participating GP independently of the researchers, to maintain the privacy of patient participants and minimize the research-related administrative burden placed on practice site staff. Assistance is offered by the PULSAR researchers in training relevant practice staff in identifying potentially eligible patients.

GPs were requested initially to identify around 50 eligible patients from their practice site. Each cluster site was originally provided with a base remuneration of $200 for committing resources to help offset administration costs involved in recruitment. An additional $25 is received by the site for the successful recruitment of each eligible patient, and an additional $25 is sent to patients who return the survey in the provided return envelopes to the researchers.

Strategies to assist participating GPs are informed by the known impediments to recruitment in general practice [40–42]. The primary mode of patient recruitment is through survey packs that are sent in mail outs or handed out by each practice site. The packs contain an invitation to participate letter, a participant information and consent form, the study instruments, and two reply-paid envelopes. These envelopes are addressed to the PULSAR team rather than to patients’ clinics in order to reduce possible breaches of confidentiality; consenting participants return their data directly to the research team, who then securely enter (using password-protected files and computers) and store (using lockable filing cabinets for hard copies) all information. GPs and/or practice managers are required to oversee the mailing or handing out of survey packs.

Recruitment strategies were designed from the start to be flexibly employed according to the needs of each practice. A number of secondary strategies were also developed to promote patient response, including offering on-site availability of researchers, advertising via practice sites, and GPs handing out information flyers to eligible patients.

Practice billing and clinical software is used to identify those patients treated by the participating GP in the previous three months who have had a mental health plan drawn up or a review of a mental health plan conducted and/or have been prescribed any class of antidepressant medication on a continuing basis (for at least a month) as treatment for a mental illness. Billing and clinical software is also used to identify patients of the participating GP who have been prescribed antipsychotic medication in the previous six months or have had a diagnosis of psychosis. The participating GP is required to screen all lists of potential participants, with reference to their clinical notes if necessary, to confirm clinical status and eligibility for the study. It is emphasized that this step is important in the identification of patients with a diagnosis of psychosis as anti-psychotic medications are also prescribed for people without such a diagnosis.

#### Challenges with patient recruitment and retention

Initial patient recruitment by the cluster sites generated mixed results that varied from one cluster site completing baseline recruitment within one week to others not reaching their target after six months. Some clusters reported difficulties in identifying potentially eligible patients and a reluctance to mail to patients in case doing so jeopardized the practice/patient relationship. Other reasons for some cluster sites not distributing the survey to patients were: confusion about patient eligibility; believing the study was over or mistakenly thinking that the cluster had withdrawn from it; a lack of interest from patients in completing the surveys; and the required increase in administrative burden. Reasons given for being unable to identify eligible patients included resource pressures or having high numbers of patients that were either under the age of 18 or from culturally and linguistically diverse (CALD) backgrounds with low English proficiency.

#### Adaptations to patient recruitment

In addition to site visits, other strategies to assist clusters include an increase in baseline remuneration to $500, identification by the Project Manager of key personnel for liaison, and reductions of the administrative burden by the provision of relevant, clinic-tailored advice. A sub-study has been established to examine aspects of recovery-oriented practice in GP clinics with high CALD patient populations.

### Procedures to minimize bias

The study GPs could not be blinded to the intervention allocation as the intervention involved GP training. Therefore, the following procedures to minimize other sources of bias have been adopted:Wherever possible, the research assistants, administration staff, and data entry staff are blinded to the intervention allocation.Patients enrolled: procedures undertaken to minimize contamination include that participating patients are not advised by the research team if their GPs has received the intervention training.Control clusters: patients in the control clusters continue to receive treatment as usual. As the study has a stepped-wedge design, all sites will receive the intervention by Step 2. Stepped-wedge designs are often preferred for such community-based pragmatic trials as they can minimize contamination of control clusters as staff and clinicians in all sites know that the study intervention is eventually coming [32–34].Recruitment: capacity to give informed consent is presumed for the majority of people and provisions are made to ensure those most in need are given the opportunity to participate. For example, the recruitment sampling method outlined above allows for maximum numbers of patients to be identified who then have a choice in deciding whether or not they would like to participate in research. This is done to assist in avoiding possible sampling bias and gives flexibility for patients to respond based on possible fluctuations in mental health. Ethics research indicates that people with serious mental illness are able to provide informed consent to participate in research, especially if particular efforts are made to recruit them [50]. Research also indicates that, for people with mental health issues, participating in research can lead to positive reactions such as a sense of enjoyment and empowerment, and is beneficial for improved service delivery [51, 52]. It is presumed that those who do not wish to participate, or those who are unable to understand the study goals and procedures, will not return the consent forms and completed measures.Allocation: all randomization was carried out by the statistician in the research team following the appropriate procedures set out earlier.In analysis: wherever possible, the data collectors and data entry team are blinded to allocation status and do not have access to information about the allocation of clusters. Study data are entered into a study database that does not contain information about intervention status.

## Statistical analyses

The recovery-oriented practice training intervention for primary care will be evaluated at the patient level by examining the surveys of adult patients who consult the participating GPs for mental health issues. The main evaluation plan is to examine the cross-sectional surveys returned by patients during three data collection periods: baseline, Step 1, and Step 2 (see Fig. 1).

The planned data collection schedule depends on the training intervention being delivered at each cluster in the scheduled month (see Fig. 1). As training delays in some clusters are expected, the following two main analysis approaches are planned to compare the post-intervention and control (pre-intervention) periods:Study planned dataset, which will use data collected from patients during the planned six-month periods centered on the midpoints of February 2015, August 2015 and November 2015 (see Fig. 1). Other data collected outside of these timespans are considered a protocol violation and are excluded from this dataset.Per-protocol all data dataset, which will use all available data time-stamped from date of intervention received at the cluster, as outlined in Table 3.

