**Methods:**

The intervention mixed methods design involves a stepped-wedge cluster randomized controlled trial testing the outcomes of training in recovery-oriented practice, together with an embedded qualitative study to identify the contextual enablers and challenges to implementing recovery-oriented practice. The project is conducted in Victoria, Australia between 2013 and 2017. Eighteen general practices and community health centers are randomly allocated to one of two steps (nine months apart) to start an intervention comprising GP training in the delivery of recovery-oriented practice. Data collection consists of cross-sectional surveys collected from patients of participating GPs at baseline, and again at the end of Steps 1 and 2. The primary outcome is improvement in personal recovery using responses to the Questionnaire about the Process of Recovery. Secondary outcomes are improvements in patient-rated measures of personal recovery and wellbeing, and of the recovery-oriented practice they have received, using the INSPIRE questionnaire, the Warwick-Edinburgh Mental Well-being Scale, and the Kessler Psychological Distress Scale. Participant data will be analyzed in the group that the cluster was assigned to at each study time point. Another per-protocol dataset will contain all data time-stamped according to the date of intervention received at each cluster site. Qualitative interviews with GPs and patients at three and nine months post-training will investigate experiences and challenges related to implementing recovery-oriented practice in primary care.

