Estimated intervention effects will be reported as the mean outcome difference for continuous outcomes and Odds Ratio for binary outcomes between intervention and control periods, assuming a constant treatment effect over time. This can be described as a meta-analysis approach as (in the case of continuous data) the mean change in each cluster will be standardized by using the variance of the outcome measure within that cluster. The estimated intervention effects will be reported with 95% Confidence Intervals and *p* values. Analysis will be conducted using Stata V.14, StataCorp. Stata Statistical Software: Release 14. College Station, TX: StataCorp LP, 2015.

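### Two differently defined datasets are both called main for the same comparison, and the primary QPR analysis is tied to neither; the as-assigned analysis should be named as the single primary

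*Protocol article*

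**What the plan says.** The Statistical analyses section states that "the following two main analysis approaches are planned to compare the post-intervention and control (pre-intervention) periods" and lists two.

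- **Planned dataset.** Surveys from the planned six-month windows only. Surveys outside the windows are treated as protocol violations and left out.
- **All-data dataset.** "Per-protocol all data dataset, which will use all available data time-stamped from date of intervention received at the cluster".

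The same section says that training delays are expected in some clusters.

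The Main analysis plan defines one primary analysis: a linear mixed model of patient-level QPR at baseline, nine months and 18 months, with intervention status and time as fixed effects. It names no dataset. The Sensitivity analyses section deals only with missing data and gives neither dataset a supporting role.

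On error control, Sample size targets has one level, "significance level set at 0.05", with no division between analyses. The Main analysis plan adds: "The estimated intervention effects will be reported with 95% Confidence Intervals".

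Three other places bear on the order. The Abstract (Methods) says "Participant data will be analyzed in the group that the cluster was assigned to at each study time point" and only then mentions a further per-protocol dataset. The section on intervention modifications and delays says that the analysis plan was widened to use all data with actual training dates. The opening of Statistical analyses describes the main evaluation in terms of the three collection periods.

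**The concern.** The two datasets differ in two respects: which surveys count, and how a survey is classed as exposed or unexposed (planned step or actual training date). Where a cluster trains late, the same survey can count as intervention in one analysis and as control in the other. The two analyses therefore estimate somewhat different effects, and they can disagree on the QPR.

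Both carry the label main, and the article does not say which one decides the trial. Someone reporting the results could rest the conclusion on whichever is more favourable without departing from the text. The single 0.05 level used for the sample size assumes one deciding test.

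The name of the second dataset adds to the difficulty. A per-protocol set normally removes data that departed from the protocol, whereas this one keeps all available data and classes them by the training actually received. That is an as-treated analysis. Of the two, it is the planned dataset that excludes protocol violations.

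**Working it through.** **Is there a stated order?** The relevant places, side by side:

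| Place in the article | What it suggests | Does it rank the two? |
|---|---|---|
| Abstract, Methods | As-assigned analysis first, then another dataset | No |
| Intervention modifications and delays | All-data approach was added to an existing plan | No |
| Statistical analyses, opening | Main evaluation uses the three collection periods | No |
| Statistical analyses, list | Both approaches are main | Gives equal standing |
| Main analysis plan | One primary QPR model at scheduled times | No dataset named |
| Sensitivity analyses | Missing data only | No |

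The exposure variable does not settle it either. Table 2 defines intervention status by whether a six-month lag has passed, without saying whether the lag runs from the planned or the actual training date.

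**What would an either-wins reading cost?** The plan gives no figure of its own for this, so there is none to reproduce.

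Inputs:
- Level 0.05 for each test (Sample size targets).
- Two-sided testing. The article does not state sidedness; this is assumed from the 95% intervals. The critical value is 1.96.
- Correlation r between the two test statistics. This is an assumption, because the overlap of the datasets is not given. It may be high, since the all-data set takes every available survey and so contains those in the planned windows.
- Each test is assumed to hold 5% on its own.

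Formula: P(at least one significant, no true effect) = 1 − P(|Z1| < 1.96 and |Z2| < 1.96), with Z1 and Z2 standard bivariate normal with correlation r.

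Bounds: with identical statistics, 1 − 0.95 = 0.05. With independent statistics, 1 − 0.95 × 0.95 = 0.0975.

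| Assumed r | P(both non-significant) | P(at least one significant) |
|---|---|---|
| 0.95 | 0.9354 | 6.5% |
| 0.9 | 0.9296 | 7.0% |
| 0.7 | 0.9165 | 8.3% |
| 0.5 | 0.9093 | 9.1% |

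**How often would the two disagree if the intervention works?** Suppose each analysis has the design power of 0.80. Then P(exactly one significant) = 2 × (0.80 − P(both significant)), counting significance in the favourable direction.

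- r = 0.95: 2 × (0.80 − 0.7646) = 0.071
- r = 0.9: 2 × (0.80 − 0.7499) = 0.100
- r = 0.8: 2 × (0.80 − 0.7290) = 0.142
- r = 0.5: 2 × (0.80 − 0.6872) = 0.226

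So even with strongly correlated analyses, roughly 7% to 10% of such trials would end with one significant result and one not.

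**The case against.** The best reply is that an order can be read from the article. The Abstract puts the as-assigned analysis first. The all-data approach is described as an enlargement of the plan. The word primary is attached to one analysis only, at scheduled time points. The article also condenses a fuller plan, and a hierarchy of analysis sets is commonly left to the statistical analysis plan, which is not shown.

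Much of this stands. The hints all point the same way, towards the scheduled, as-assigned analysis. The absence of a rule for discordant results would not be a finding on its own. What remains is that the article itself gives both approaches the same label and connects the primary model to neither. That is a choice stated on the page, not a detail left out.

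Three stronger readings are tempting, and the article does not support them.

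- *The trial has two primary p-values, so the 0.05 level is lost.* Main is not the same word as primary, and nothing says that success may be claimed on either result. The inflation arises only if the plan is read that way.
- *Randomisation gives the second analysis no protection.* Clusters were randomised to a step, and the step should still largely determine when training took place. Departures from it are not randomised, so the protection is weakened but not removed.
- *Practices caused the training delays, so exposure timing reflects practice characteristics.* The article reports delays in training without giving that cause. It is a possible source of bias, not a documented one.

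**Conclusion.** The point holds as a defect of specification. Two datasets with different exposure definitions are given equal standing for one comparison at a single 0.05 level, and the leading role of the as-assigned analysis can only be inferred.

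If a positive result on either were taken as success, the two-sided false-positive rate would exceed 5% and could not pass 9.75%; with strongly overlapping data it would be nearer the lower end. This rests on the assumed correlations, on two-sided testing, and on each test being valid alone. The last assumption is the weakest for the as-treated analysis. The figures therefore cover multiplicity only and do not measure any bias from non-random training dates.

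The per-protocol label is wrong for a set that keeps all data and classes them by actual training date.

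**What to change.** In Statistical analyses, name the analysis by assigned step, in the planned windows, as the single primary analysis of the QPR on which the conclusion rests, and repeat that dataset in the Main analysis plan where the primary model is defined. Rename the other *as-treated, all data* and describe it as supportive. Report the number of surveys whose exposure status differs between the two, so that readers can see how far the analyses could diverge.

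The cost is wording and one count; no new data are needed. The downside is that the larger all-data set can no longer carry the primary conclusion.

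Keeping both as main and testing each at 0.025 would also control the error rate, but at a price. With critical value 2.241 in place of 1.960, an effect detectable with power 0.80 would be detected by a given analysis with power Φ(1.960 + 0.842 − 2.241) = Φ(0.561) ≈ 0.71. Ranking the two avoids that loss.
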